## Methods

### Study design

This study will use a nested mixed-method study with a quantitative survey and a qualitative interview to gain a better understanding of the effect and acceptability of the AI and mHealth-based intervention program for T2DM. The research will take place from August 2023 to June 2025. The quantitative survey will be conducted as a community-based cluster randomized controlled trial with two parallel groups to compare the effectiveness of the AI-HEALS-based education program on T2DM control and self-management behaviors (such as medication use, dietary and physical activity modification). The intervention will last three months. Questionnaires, physical examinations, and personal in-depth interviews (the qualitative study) will be conducted to participants at baseline, 1, 3, 6, 12, and 18 months to examine changes in self-management behaviors and blood glucose control. Cost-effectiveness analysis will be conducted at 12 and 18 months. The flow chart for the study shown in Figs. 1 and 2.

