### Study setting and randomization

The study will be conducted in 40-45 community health centers (CHCs) in Beijing, China, as the unit of randomization. The community health center contains 8-10 people with T2DM. A computer-generated list of random numbers will assign clusters (CHCs) in a 1:1 ratio to an intervention group and a control group. All subjects in each cluster will receive the same intervention (SDPC plus AI-HEALS) or control (SDPC). Blinding of the participants or researchers cannot be guaranteed considering the nature of the intervention. The proportion of sociodemographic characteristics (such as gender, age, and location) between two groups will be evaluated at baseline to verify that the data are balanced and comparable. Study designer will generate the allocation sequence, CHCs staff will enroll participants, and study designer will assign participants to interventions.

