### Effect size

Based on our previous study, assuming an alpha risk of 0.05, a beta risk of 0.10, an intraclass correlation (ICC) of 0.002, a mean level of HbA1c in patients with type 2 diabetes of 7.13%, and a standard deviation (SD) of 1.60%, at least 2 clusters, and 166 subjects (138 total before considering a dropout rate of 20%) in each cluster are expected to be recruited according to the sample size formula for unmatched studies [66] to detect a decrease in HbA1c to 6.50% after the intervention. As a result, a total of 664 patients in 4 communities are required to be recruited for this program.

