
All user data will be kept confidential. Participants have the option to withdraw from the study at any time. Adverse events related to the intervention will be recorded and reported in accordance with local procedures.

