### Outcomes

Primary outcome: Change of HbA1c from baseline to 1, 3, 6, 12, and 18-month follow-up.

Secondary outcomes:1. Modifications of self-management behaviors: dietary, physical activity, blood glucose monitoring, and medication adherence.2. Social cognition and psychology: diabetes health literacy, self-efficacy, depression, anxiety and stress.3. Metabolic control: self-reported fasting plasma glucose or 2 h plasma glucose, dose of insulin and medicine, other indicators such as blood pressure, blood lipids, and BMI.4. Economic evaluation: A comparison of incremental cost-effectiveness ratios (ICERs) will be conducted between the AI-HEALS-based intervention and usual care of T2DM. Therefore, health-related quality of life (HRQoL), healthcare utilization, including medical consultations, use of healthcare (outpatient, hospitalized, and primary care services), medicine purchases, accident visits, and direct non-medical costs (diabetes-related transportation, lodging) will be collected.

Additionally, the rate of recruitment and drop-out, as well as the reasons for drop-out, will be gathered. To determine whether the data is homogeneous, demographic characteristics and study outcomes will be compared between people dropping out and participants resistant to the entire trial during data analysis.

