### Study management

Prior to the study, the investigators will be trained and assessed comprehensively. Throughout the study, the study subjects will be registered and coded to minimize the occurrence of missing visits during the follow-up period. To maintain consistency between the intervention and control groups, survey time and questionnaire will be kept substantially identical. During data analysis, a double-entry checking procedure will be implemented to enhance the quality of data entry, and experts will be consulted to select appropriate statistical methods. If finding abnormal values, the original questionnaires will be checked and verified for accuracy to proceed to the analysis. Additionally, the qualitative data will be collated and proofread by two researchers to ensure reliability in the analysis of the qualitative findings.

The research leaders and primary investigators will supervise research implementers regularly to ensure the correct implementation of all research procedures and to guarantee the accuracy of the collected data. If investigators are failure to adhere to predefined survey and follow-up standards, research leaders will terminate the trial, revise the randomization scheme and recollect data after the modification is completed. In the event of fundamental or widespread design errors or inaccuracies in the research questionnaire during the survey process, the researchers will halt the trial to modify and redesign the questionnaire. After the necessary revisions were completed, the revised questionnaire will be then redistributed to participants.

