The data monitoring committee (DMC) will be composed of at least two members from the Biomedical Ethics Committee of Peking University, who have no conflicts of interest with our study. The DMC will conduct regular monitoring and review of the study, and will report the findings to the Ethics Committee. This process will operate independently of the primary investigators. If the DMC identifies deviations from the approved research protocol or unauthorized changes to the study procedures during the research process, they have the authority to suspend or terminate the study. Furthermore, during the research, the project researchers are responsible for promptly reporting any serious adverse events (SAE) or adverse events (AE) to the Ethics Committee. If any participants experience AE or SAE, regardless of their relationship to the research intervention or whether the intervention has been implemented, the researchers must notify the investigators within 24 h of the event and terminate the trial. Additionally, in the event of serious program bugs or significant deficiencies in user interaction during the participant's engagement with AI, the researchers must interrupt the trial, redesign the study, and rectify the issues with the AI program.

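### The adverse-event rule, as written, terminates the whole trial at the first AE or SAE of any kind, in conflict with the plan's own reporting statement and its 18-month primary outcome

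*Protocol article*

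**What the plan says.** The rule is in the last part of Study management. Its trigger is an AE or SAE in any participant, "regardless of their relationship to the research intervention or whether the intervention has been implemented". The required action is that "the researchers must notify the investigators within 24 h of the event and terminate the trial". The wording is mandatory.

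Other parts of the protocol article bear on it:

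- **End of the Intervention section:** "Adverse events related to the intervention will be recorded and reported in accordance with local procedures". Nothing there mentions stopping.
- **Study management, on investigators who miss survey standards:** "research leaders will terminate the trial, revise the randomization scheme and recollect data after the modification is completed". Here termination is followed by a fresh start.
- **Study management, other actions:** the article uses different verbs elsewhere. The trial is halted for questionnaire errors and interrupted for program bugs, and the DMC may suspend or terminate for protocol deviations.
- **Outcomes:** the primary outcome is "Change of HbA1c from baseline to 1, 3, 6, 12, and 18-month follow-up".
- **Study design:** "The research will take place from August 2023 to June 2025".

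**The concern.** The rule has no threshold. A minor, unrelated event in a control participant triggers the same action as a serious event caused by the intervention. It also contradicts the Intervention section, which treats even related events as matters for recording and reporting.

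The plan itself expects such events. The economic evaluation is to cost hospital care and accident visits at 12 and 18 months, and the skills and self-efficacy scales ask about handling hypoglycaemia. An admission or accident would ordinarily count as an AE or SAE, so under this rule the first one would end the study that is meant to cost it.

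If the rule is followed, long-term HbA1c data are lost for a reason that may say nothing about AI-HEALS. If it is not followed, the team departs from its own protocol, and whether to stop is decided case by case in a trial where blinding is not guaranteed.

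**Working it through.** **Inputs from the protocol article**

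- Size from Effect size: "a total of 664 patients in 4 communities are required to be recruited for this program". The figure reproduces: 138 × 1.2 = 165.6, rounded up to 166 per cluster, and 4 × 166 = 664.
- Size from Study setting and randomization: 40 to 45 centres, and "The community health center contains 8-10 people with T2DM". This gives 40 × 8 = 320 to 45 × 10 = 450.
- Follow-up: 18 months (1.5 years).
- Window: August 2023 to June 2025 = 5 + 12 + 6 = 23 months. A fresh 18-month run can therefore start only in the first 23 − 18 = 5 months.
- AE rate: not given. It is treated as an assumption below.

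**Person-years at risk:** 320 × 1.5 = 480; 450 × 1.5 = 675; 664 × 1.5 = 996.

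**Model.** Recorded AEs and SAEs of any cause follow a Poisson process with rate *r* per person-year. All participants are followed together for the full period.

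**Permanent closure.** P(finish) = exp(−*r* × person-years). Setting this to 0.5 gives *r* = ln 2 / person-years:

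- 0.693/480 = 0.144 per 100 person-years
- 0.693/675 = 0.103
- 0.693/996 = 0.070

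Losing the whole 20% dropout allowance on day one divides these by 0.8, giving 0.18, 0.13 and 0.09.

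**Full restart within the window.** Let *m* be the expected events per month over all participants. The first run succeeds with probability exp(−18*m*). Restarts in the first 5 months number 5*m* on average, and each succeeds with the same probability. No two runs can both succeed, because 18 exceeds 5. So P(finish) = exp(−18*m*)(1 + 5*m*). Setting this to 0.5 gives 18*m* = 0.921:

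- 0.921/480 = 0.192 per 100 person-years
- 0.921/675 = 0.136
- 0.921/996 = 0.092

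**Sensitivity to the assumed rate.** The last column is the chance of an event-free first 3 months, exp(−*r* × N × 0.25).

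| Rate per 100 person-years | N | Finish 18 months, no restart | With restarts | Event-free to 3 months |
|---|---|---|---|---|
| 0.1 | 320 | 62% | 70% | 92% |
| 0.1 | 450 | 51% | 61% | 89% |
| 0.1 | 664 | 37% | 47% | 85% |
| 0.5 | 320 | 9% | 15% | 67% |
| 0.5 | 450 | 3% | 7% | 57% |
| 0.5 | 664 | 0.7% | 1.6% | 44% |
| 1 | 320 | 0.8% | 1.9% | 45% |
| 1 | 450 | 0.1% | 0.3% | 32% |
| 1 | 664 | 0.005% | 0.02% | 19% |

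Example, N = 320 at 1 per 100: exp(−4.8) = 0.0082. With restarts, *m* = 3.2/12 = 0.267, so 0.0082 × (1 + 1.33) = 0.019. To 3 months, exp(−0.8) = 0.45.

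**The case against.** **The rate is assumed.** A reader might infer that the trial has almost no chance of finishing. The article does not support that without conditions: it gives no AE rate, and at 0.1 per 100 person-years with 320 participants the chance is 62%. This objection stands, and the size has to be stated conditionally.

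**Only recorded events count.** Table 1 lists no AE item, and the Intervention section speaks only of related events. The operative rate could be well below the true all-cause rate. This also stands, which is why the limits above refer to recorded events.

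**Participant-level withdrawal may have been meant.** The trigger is an event in a person, individual withdrawal is provided for elsewhere, and the English is uneven. A slip is realistic, and on that reading the calculation falls away. But the text names the trial. Removing everyone with any AE would also make loss depend on health and sit badly with intention to treat. It would use up the 20% dropout allowance by itself at −ln(0.8)/1.5, about 15 first events per 100 person-years. The clause would still need rewriting.

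**Termination may not be permanent.** Permanent closure is a tempting inference, but Study management uses the same verb once for a stop followed by new data collection, so it is not certain. A full restart was therefore calculated and helps little. A pause followed by continuation was not modelled, and the 5-month limit would not apply to it in that form. The separate use of other verbs for halting, interrupting and suspending argues against that reading without excluding it.

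**Not all data are lost.** The intervention lasts 3 months, and the 3-month HbA1c could often be collected. This stands: the loss falls mainly on the later visits.

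**Detail may sit in the full protocol.** Graded AE handling often does. The point here is a rule that the article states, not detail that it leaves out.

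**Conclusion.** Wrong as written. The rule ends the trial at any AE or SAE in either arm, contradicts the article's other AE statement and cannot be squared with an 18-month primary outcome.

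The size holds under three conditions: the trial-level reading, Poisson events with full simultaneous follow-up, and a recorded all-cause rate that the article does not supply. An even chance of finishing then needs at most 0.14 (N = 320) to 0.07 (N = 664) per 100 person-years, or 0.19 to 0.09 with full restarts. For AEs of any grade and cause in adults with type 2 diabetes aged up to 75, rates that low seem unlikely if events are captured, but that is a judgement and not a figure from the article.

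A reader might also infer that the DMC has no power to act on harm. The article names protocol deviations and unauthorized changes as its grounds but does not say that these are the only ones, so no such defect is claimed.

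**What to change.** In Study management, delete the instruction to terminate the trial and state instead that:

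1. all AEs and SAEs in both arms are reported, SAEs within 24 hours;
2. non-serious events judged unrelated are recorded only, and the participant stays in follow-up;
3. SAEs of any cause, and any event judged related to AI-HEALS, go to the existing DMC or Ethics Committee, which decides whether to suspend or terminate.

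Reword the AE sentence at the end of the Intervention section to cover the same events.

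The cost is a few sentences, with no new visits, survey items or committee. The downside is that an automatic stop becomes a committee judgement.

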### Intervention

#### Control arm: SDPC for patients with T2DM

Participants in the control group will receive standard health care from community doctors, including medical counselling, regular follow-up, assessment, health education, referral advice and medical examination. 

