#### Intervention arm: SDPC plus AI-HEALS-based T2DM online health education program

Participants will receive SDPC plus AI-HEALS-based intervention through the WeChat service platform "PKU Diabetes Butler" on their mobile phones, which consists of four components:1. KBQA for T2DM knowledge. Participants will be encouraged to interact with a FAQRobot (Frequently Asked Questions Robot) to accurately and efficiently gain detailed knowledge about T2DM diet (recommended or not recommended foods, food nutrients, calories, glycemic index, and glycemic load), exercise (recommended or not recommended exercise, the metabolic equivalent of physical activities), and medication management (types of medicines and how to take them), removing time and distance limitations to health care consultations and increasing health care accessibility. In addition, the FAQRobot has an entertainment function, which can tell jokes and play games with patients to calm them down. After reviewing guidelines, professional literature, and consulting experts, we identified the source material and knowledge for the T2DM self-management KQBA. Subsequently, we uploaded the underlying data to the Bot Factory^22^ Dialogue AI Platform produced by Emotibot [67], which formed an automated Q&A bot with semantic understanding and automatic knowledge mining. The Q&A bot was linked to the WeChat platform "PKU Diabetes Butler". The backend stores the questions that participants asked as well as their usage behaviors (such as time and frequency) so that we can improve the knowledge graph regularly and assess the usage patterns of participants.2. Recording and monitoring of physiological indicators as well as lifestyle behaviors. Participants will be encouraged to record information on physiological indicators (blood glucose, blood pressure), diet, physical activity, and medication-taking regularly on the platform, which stores and uploads the records electronically and enables long-term monitoring of blood glucose control and changes in self-management behaviors.3. A reminder service for taking medications and monitoring blood glucose levels. Participants will be encouraged to enter the time they want to be reminded in the system, and the platform can remind them to take their medication or monitor blood glucose levels at specified time.4. Automated and personalized messaging about diabetes self-management. Participants will receive 1–3 automated messages about T2DM control and management per week, the content of which will be based on multi-theory model (MTM) of health behavior change, and will contain knowledge of T2DM diet, exercise, and medication taking to increase health literacy and to encourage behavioral change. Furthermore, based on the questions users ask the FAQRobot, the system will accurately push additional, tailored articles. Researchers will also regularly log into the backend to check the number, type and time of articles read by the participants in order to tailor the content and frequency of messages to their reading patterns.

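### A fault in the AI program, which only the intervention arm can produce, obliges the researchers to redesign the study rather than repair the software under a fixed design

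*Protocol article*

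**What the plan says.** The rule is in the protocol article, Study management. Its trigger is "in the event of serious program bugs or significant deficiencies in user interaction during the participant's engagement with AI". Its consequence is that "the researchers must interrupt the trial, redesign the study, and rectify the issues with the AI program". It names three separate actions, and all three are mandatory.

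Other sections settle who can trigger the rule and who acts on it. In the intervention arm, "Participants will receive SDPC plus AI-HEALS-based intervention through the WeChat service platform". In the other arm, "Participants in the control group will receive standard health care from community doctors", with no AI component. Under Study setting and randomization: "Blinding of the participants or researchers cannot be guaranteed considering the nature of the intervention".

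The third specific objective (end of Background) includes the acceptability of the programme. The Qualitative analysis section plans interviews on acceptability, usability and satisfaction at 1, 3, 6, 12 and 18 months. The Statistical analysis section adopts intention to treat.

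Study management has a second, similar rule for survey instruments. If the questionnaire has fundamental or widespread errors, "the researchers will halt the trial to modify and redesign the questionnaire", and "the revised questionnaire will be then redistributed to participants".

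**The concern.** Repairing a serious software fault is legitimate. The difficulty is the additional duty to redesign the study. A randomised comparison is protected by fixing allocation, participants, baseline, outcomes and visits before anyone sees how the arms fare. This rule reopens all of these without saying which may change, and it does so on information that can come from one arm only.

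The second limb of the trigger makes this worse. A program crash is recognisable. Whether shortcomings in user interaction count as significant is a judgement, left to people who may know the allocation and who, according to the description of the intervention, look at usage in the backend. Poor interaction is also something the study wants to learn about, so the rule can turn a finding into a reason to change the study.

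What is at stake is whether the comparison reported at the end is the one that was randomised.

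**Working it through.** The point concerns a rule of conduct and rests on no sample size, power or error rate, so there is no figure to reproduce. The check sets the passages side by side.

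1. **Is the action mandatory?** Yes. The researchers are told that they must act, and redesigning the study is listed separately from putting the AI program right. The wording therefore goes beyond software repair.

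2. **Can either arm trigger it?** No. The trigger arises while a participant is using the AI. The intervention arm receives standard care plus AI-HEALS and the control arm receives standard care alone, so nothing in the control arm can set the rule off.

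3. **Is there a threshold?** No. Neither a serious bug nor a significant deficiency is defined, and no number of users, duration or type of fault is given.

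4. **Who decides?** The researchers. Their blinding is not guaranteed. The Intervention section also has researchers log in regularly to see what participants read. The data monitoring committee described in the same paragraph is given no part in this particular decision.

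5. **Does the trigger overlap with what is evaluated?** Yes, in its second limb. Usability, acceptability and satisfaction are interview topics at 1, 3, 6, 12 and 18 months, and acceptability is in the third objective. Evidence of poor interaction would thus emerge during the trial as part of its planned data collection.

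6. **What stays fixed after a redesign?** The text does not say. Intention to treat governs how randomised participants are analysed, but the AI-fault rule does not state that allocation, participants, baseline, outcomes or schedule are preserved.

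7. **Which way would any bias run?** This depends on the missing statement.
   - If data from the faulty period were set aside or participants restarted, the estimate would describe the repaired product and could favour the intervention.
   - If those data were kept, faults and interruption would more likely dilute the effect.
   - The text supports neither reading over the other. The neighbouring rule on investigators who depart from survey standards expressly provides for data to be collected again; the AI-fault rule contains no such words.

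8. **Questionnaire rule, for comparison.** Its trigger is a fundamental or widespread error, which is a high bar, and it can arise in either arm. Study management also says that survey timing and questionnaires are to be kept substantially the same in both groups. HbA1c, the primary outcome, is measured in venous blood and is unaffected. What remains is that a revised form issued mid-trial makes within-person change harder to interpret on the scale concerned.

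**The case against.** The strongest reply is that this is an emergency clause for serious faults, that such faults have to be corrected, and that a condensed article need not spell out how data are handled by software version. Much of that stands. Repair is proper, and the absence of a version-handling rule would not be a finding on its own. But the article does not merely leave a detail unsaid: it states a duty to redesign the study, and that wording is the defect.

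A reader might infer more than the documents support:

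- **That an ineffective intervention would be replaced instead of evaluated.** The trigger is a serious technical or interaction fault. A weak or null effect on HbA1c does not set it off.
- **That the rule biases the result towards effectiveness.** This needs early data to be discarded or participants restarted. The rule says neither, and intention to treat is the stated principle.
- **That the rule contradicts the intervention's description, where user questions are stored "so that we can improve the knowledge graph regularly".** Routine updating of content and a special rule for serious faults can coexist.
- **That a redesign is likely.** The article gives no fault rate, so any probability would rest on an invented input.
- **That the questionnaire rule undermines all secondary outcomes or takes a new baseline after exposure.** Many scales are published instruments, the rule is not specific to an arm, and the text says only that the revised form is redistributed.

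**Conclusion.** The point holds in a limited form. The article obliges researchers whose blinding is not guaranteed to redesign the study on an undefined trigger that only the intervention arm can produce and that overlaps with the usability and acceptability under evaluation. Followed literally, this allows the design to change mid-trial in response to one arm's experience, so that the final comparison may not be the one randomised.

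Neither the probability of this nor the size of any bias can be calculated from the document, and the direction depends on how earlier data are treated. The conclusion assumes that the sentence means what it says. If the authors meant only that the software would be repaired, the wording should say so. The harm is contingent on a fault occurring, but the correction is cheap enough that it should be made. The questionnaire rule is a side issue.

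**What to change.** In Study management, replace the words that require the study to be redesigned with wording to this effect: *Faults in the AI program are repaired and logged with date and software version. Allocation, participants, original baseline values, outcomes and visit schedule remain unchanged. All randomised participants are analysed by intention to treat, with a sensitivity analysis by software version.* Any suspension for safety stays where the protocol now puts it.

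As a side note on the questionnaire rule: finalise the instruments before randomisation. If a later correction is unavoidable, introduce it in both arms at the same visit, keep the original baseline and flag the version in the analysis.

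The cost is a change of wording, a version log and one sensitivity analysis. The article states that recruitment had not begun when it was written. The downside is that some data will come from an imperfect early version of the program, and these data then count in the result.
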